
It has not yet been examined whether cognitive-motor training including spatial orientation tasks is suitable to increase PA, enlarge LS mobility and to improve spatial orientation and, as a consequence, elicit changes in well-being and general cognitive-motor functioning in nursing home residents. Against this background, the overall goal of this multicentric RCT (PROfit) is to investigate the efficacy of three different intervention approaches on PA, LS mobility, and spatial orientation: The *PROfit basic* group will perform functional strength, balance, flexibility, and walking exercises at the same location, while the *PROfit plus* group relocates three times during the training. The *PROfit orientation* group receives navigation tasks in addition to the relocation during interventions. We hypothesize that all three intervention arms will generate slower decline or even improvements in residents’ PA, LS mobility, and spatial orientation compared to a wait-list control group. We assume that *PROfit plus* will be more effective than *PROfit basic* because of residents’ improved orientation due to the different training locations. Furthermore, we expect the *PROfit orientation* intervention to be most beneficial due to its additional focus on spatial orientation.

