### Trial design

Based on the existing research and the physical training recommendations mentioned above, a multicenter intervention study will be conducted, aiming to determine the feasibility and efficacy of three different exercise intervention programs for residents of nursing homes. The type of intervention program will be randomly assigned to the participating nursing homes. The participants’ allocation to the intervention or wait-list control group will be randomized after baseline assessment in each nursing home. The assessment of primary and secondary outcomes will take place upon entry to the study (T1) by a blinded assessor and will be repeated at twelve (T2) and at 24 weeks (T3) (see Table 1).

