Overall, the exercise programs will be continuously adapted to the residents’ capacity and organized as a progressive challenge to expand participants’ resources. This will be done following the FITT principle (Frequency, Intensity, Time, Type) [94] and the recommendations of Herold and colleagues [39] to establish a cognitively beneficial program. These recommendations refer to a regularly performed sequence of structured and progressive physical exercises that are adapted to individuals’ performance limits [39]. Given the different pre-conditions of the participants, adaptions in different domains (e.g. physical or cognitive) are non-linear; trainers have to constantly adjust the program to participants’ abilities. Participants in the wait-list control group will be asked to continue their regular everyday activities for twelve weeks until they receive the intervention type which was randomly assigned to the nursing home (cf. Fig. 2).

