### Data collection, management, and analysis

#### Statistical analysis

Descriptive data will be reported as group mean values and standard deviations or medians and interquartile ranges depending on the type of outcome and their distribution. Analysis of baseline differences will be performed using a multivariate analysis of variance (MANOVA). Parametrical and normally distributed measures will be analyzed in separate 4 (group: PROfit basic, PROfit plus, PROfit orientation, wait-list control group) × 3 (test: baseline assessment, post-allocation, close-out-testing) analyses of variance (ANOVA) with repeated measures. If baseline differences are detected, baseline assessment values as well as age and sex discrepancies will be included as covariates in the statistical model. In the case of statistically significant interaction effects, Bonferroni-adjusted post-hoc tests (t-tests, Wilcoxon tests) will be performed to detect statistically significant differences in the groups between baseline- and post-allocation-testing. Kruskal-Wallis and Friedman tests instead of ANOVA will be used for non-parametrical variables and for data for which normal distribution could not be assumed. The effect size will be determined using Cohen’s *f* [95] which is indicative of the effectiveness of treatment and helps to assess whether a statistically significant difference is of practical concern. Cohen’s *f* values are classified as small (0 ≤ *f* ≤ 0.24), medium (0.25 ≤ *f* ≤ 0.39), or large (*f* ≥ 0.40). Additionally, PS_dep_ scores (probability of superiority for dependent samples) will be computed as an estimate of effect size in non-parametrical post-hoc tests [96]. The significance level will be set at *p* < 0.025.

Intention-to-treat analysis will be conducted. For this purpose, data of all participants will be processed in the groups into which they were randomly assigned, regardless of whether they received or adhered to the assigned intervention. The majority of participants are expected to take part in a minimum of 80% of the training sessions. An additional per-protocol analysis will be performed if a sufficient number of participants are lost to outcome assessment or insufficient participation in training sessions. Multiple Imputation will be used to handle missing data assuming that data are missing by chance.

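### The group-by-test interaction includes week 24, after the wait-list group has been offered training, so it does not isolate intervention versus untreated control

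*Protocol article*

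**What the plan says.** The Trial design section sets assessments at entry (T1), twelve weeks (T2) and 24 weeks (T3). The Interventions section says that wait-list residents will "continue their regular everyday activities for twelve weeks until they receive the intervention type which was randomly assigned to the nursing home". The programme itself runs for twelve weeks, so by T3 the wait-list group has been offered it and may just have finished it.

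The Background states the hypothesis for all three programmes as "slower decline or even improvements in residents’ PA, LS mobility, and spatial orientation compared to a wait-list control group".

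The Statistical analysis section tests this in a four-group design with three levels of "test: baseline assessment, post-allocation, close-out-testing) analyses of variance (ANOVA) with repeated measures". Post-hoc tests follow "In the case of statistically significant interaction effects". They are Bonferroni-adjusted and look for "statistically significant differences in the groups between baseline- and post-allocation-testing". For non-parametric post-hoc tests the effect size is the "probability of superiority for dependent samples". The significance level is 0.025.

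The Sample size section powers the trial on the same interaction, with four groups and three measurements.

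**The concern.** Only the change from T1 to T2 compares trained residents with untreated ones. From T2 to T3 the roles reverse: the initially trained groups have stopped and the wait-list group is offered training. Because the wait-list group is pooled across homes, at T3 it also mixes all three programmes.

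An interaction over T1, T2 and T3 asks whether the four group profiles differ in any way. It can be significant because of what happens after crossover, and it can be diluted when the wait-list group partly catches up. Since it decides whether post-hoc tests are run, the conclusion on efficacy would hang on a test that does not target the hypothesis.

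**Working it through.** **The plan's own figure.** Inputs from the Sample size section: f = 0.15, alpha 0.05, power 0.95, k = 4 groups, m = 3 measurements, r = 0.60, dropout 30%. I used the within-between interaction formula, lambda = f²·N·m/(1 − r), with (k − 1)(m − 1) = 6 and (N − k)(m − 1) degrees of freedom and sphericity assumed.

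- N = 127 is the smallest that reaches 0.95; four equal groups need 128. Then lambda = 0.0225 × 128 × 3 / 0.4 = 21.6, and power is 0.952.
- 128 × 1.3 = 166.4, so 167 per centre and 501 over three centres. The article states 171 and 513, a difference of under 3%.
- Dividing by 0.7 instead gives 183 per centre and 549, which does not match.

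So 513 is approximately reproduced as a per-centre figure times three, and it rests on the interaction that includes T3.

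**What the interaction responds to.** Inputs:

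- completers N = 513 × 0.7 = 359
- control share w = 0.25, from four equal groups (42–43 each per centre)
- r = 0.60 and alpha 0.025
- d, the common standardised difference between each trained group and wait-list. The article does not give it, so I show 0.3 to 0.5 as an assumption.
- participants treated as independent

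For a difference profile over T1, T2, T3, let S be the sum of squared deviations of the profile from its own mean, in units of d². Then lambda = N·w·(1 − w)·S·d²/(1 − r), with 6 and 710 df. For T1–T2 alone S = 0.5, with 3 and 355 df.

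Example at d = 0.4 with profile (0, d, 0): S = 2/3, so lambda = 359 × 0.1875 × 0.6667 × 0.16 / 0.4 = 17.95.

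| Test and true difference profile | S | Power at d = 0.3 / 0.4 / 0.5 |
|---|---|---|
| 4×3, (0, d, d): control stays untreated, effect lasts | 2/3 | 0.54 / 0.85 / 0.98 |
| 4×3, (0, d, 0): effect at T2, full catch-up | 2/3 | 0.54 / 0.85 / 0.98 |
| 4×3, (0, 0, d): no effect at T2, difference at T3 only | 2/3 | 0.54 / 0.85 / 0.98 |
| 4×3, (0, d, d/2): effect at T2, half catch-up | 1/2 | 0.39 / 0.70 / 0.91 |
| T1–T2 interaction only, (0, d) | 1/2 | 0.51 / 0.81 / 0.96 |

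The first three rows are indistinguishable to the test, although in the third nothing happened in the controlled period. In the fourth row, noncentrality equals that of the T1–T2 test but is spread over 6 instead of 3 numerator df, which costs about 5 to 12 points.

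**An extreme case.** If trained groups lose all their gain and the wait-list group gains the same amount, the profile is (0, d, −d) and S = 2. Noncentrality is then 0.94·N·d², against 0.31·N·d² for (0, d, 0), so two thirds of it arises after crossover. Nothing in the article makes this profile likely.

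**The case against.** The strongest reply is that the post-hoc tests are restricted to baseline versus post-allocation, so T3 never enters follow-up testing. That is true and it lessens the problem. It does not remove it. On the ANOVA route these tests wait for the mixed interaction, and their wording, together with a dependent-samples effect size, reads as change within each group. The article names no between-group contrast at T2.

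Several stronger readings are tempting, and the article does not support them.

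- *The interaction says nothing about intervention versus control.* Too strong. If training has no effect at any time, type I error is kept. Significance caused by controls improving once trained would itself hint that training works, though not through the randomised contrast. A difference at T3 only needs either a delayed effect or training that helps the wait-list group but not the original arms.
- *Including T3 is what costs power.* Not in general. At d = 0.3 with full catch-up, the planned test has 54% power and the T1–T2 interaction 51%. A T2 comparison adjusted for T1 has 63% (3 df), or 80% with the three programmes pooled (1 df). Those gains come from baseline adjustment and pooling: a pooled two-group analysis that keeps T3 already reaches 73%.
- *The plan will report T3 differences as efficacy against untreated control.* It does not say so.
- *The interaction gates every outcome.* Non-normal and non-parametric variables go to Kruskal-Wallis and Friedman tests, where no such gate is stated.

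A separate analysis plan may name a primary time point and contrasts. That would not change the test, its three levels and the gate that this article fixes.

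**Conclusion.** The point holds in this form: the ANOVA gate does not isolate the hypothesis of intervention versus untreated wait-list control, because one of its three levels falls after crossover. A significant result can come from post-crossover change alone, with probability 0.54 to 0.98 for a T3-only difference of 0.3 to 0.5 SD. A null result is also harder to read under partial catch-up, with a loss of about 5 to 12 points against the T1–T2 interaction at half catch-up. Full catch-up costs no power against that test.

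The timing conflict is certain from the text. The sizes rest on the assumed d, equal groups, 30% dropout, sphericity and independent participants. Programme type is randomised by home, so the independence assumption is a simplification.

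**What to change.** Name the between-group comparison at T2, adjusted for T1, as the confirmatory test: each programme against wait-list, with the multiplicity adjustment stated. Do not make it conditional on an interaction that includes T3. Comparisons between programmes can follow as their own pre-specified contrasts.

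Analyse T3 separately and label it as two things: maintenance from T2 to T3 in the initially trained groups, and a non-randomised T2–T3 change in the wait-list group once it is offered training. State that T3 group differences are not a comparison with untreated control.

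The sample size statement should then be restated for the T2 comparison at the significance level used in the analysis, since it now uses three measurements and alpha 0.05 while the analysis uses 0.025.

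The cost is analysis wording and one recalculation. No visit, measurement or participant is added, and all T3 data are still used.

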#### Assignment of interventions

To avoid selection bias, stratified randomization will be conducted to divide participants into an intervention group and a wait-list control group. The random allocation will be stratified according to sex, age, and cognitive performance to avoid differences in the baseline conditions between the groups. Data collection will be done by blinded assessors; data will be stored securely and in pseudonymized form using a coded ID number to maintain participants’ confidentiality. To avoid performance bias, the measurements and the interventions follow a standardized protocol.

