#### Sample size estimate / power calculations

The required sample size was calculated with G*Power (Version 3.1.9.2, Heinrich Heine University of Duesseldorf) [97]. The following input parameters were used to obtain small-sized test × group interaction effects: effect size (f = 0.15), type I error (α = 0.05), type II error (1-β = 0.95), number of groups (*n* = 4), number of measurements (*n* = 3), correlation between measurements (r = 0.60). Additionally, a dropout rate of 30% (i.e., 20% lost to follow-up; plus 10% deceased) was considered. Our analysis resulted in a total sample size of 513 participants (i.e., 171 per center with 42–43 participants allocated to each group).

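### Adjustment for baseline, age and sex depends on a baseline significance test, and baseline would then be both covariate and outcome; the cost is precision and pre-specification

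*Protocol article*

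**What the plan says.** The Statistical analysis section of the protocol article sets out three linked steps.

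- A baseline test: "Analysis of baseline differences will be performed using a multivariate analysis of variance (MANOVA").
- A main model with four groups and three occasions, in which baseline is an outcome level: "test: baseline assessment, post-allocation, close-out-testing) analyses of variance (ANOVA) with repeated measures".
- A rule that joins the two: "If baseline differences are detected, baseline assessment values as well as age and sex discrepancies will be included as covariates in the statistical model".

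No threshold is given for the baseline test alone; the only general statement is "The significance level will be set at *p* < 0.025". Outcomes that are not normally distributed go to Kruskal-Wallis and Friedman tests.

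Under Assignment of interventions, "The random allocation will be stratified according to sex, age, and cognitive performance". Under Trial design, the type of program is randomised to nursing homes, and residents are then randomised to intervention or wait-list within each home.

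**The concern.** A significance test at baseline is the wrong instrument for choosing covariates. In a randomised comparison it mostly measures chance. It says nothing about whether a variable predicts the outcome, which is what makes adjustment worthwhile. The protocol already assumes that baseline is strongly prognostic, since its sample size rests on a correlation of 0.60 between measurements.

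The rule also leaves the main model open until the data are seen, and the two candidate models can give different answers. If the rule fires, baseline is regressed on itself at one of the three occasions. Finally, the design balances on sex, age and cognitive performance, but the analysis admits sex and age only conditionally and does not name cognitive performance as a covariate. At stake are power and a fixed primary model.

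**Working it through.** **Inputs.** From Sample size estimate / power calculations: "effect size (f = 0.15), type I error (α = 0.05), type II error (1-β = 0.95"), four groups, and "number of measurements (*n* = 3), correlation between measurements (r = 0.60"). From Statistical analysis: significance level 0.025. Residents per home and the intraclass correlation (ICC) are not given, so they are assumptions below.

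**The plan's own figure.** For the group-by-test interaction, with sphericity assumed, the noncentrality is N·m·f²/(1−r), with 6 and 2(N−4) degrees of freedom. At f = 0.15, m = 3, r = 0.60, alpha 0.05 and power 0.95 this gives N = 127, or 128 in equal groups. Then 128 × 1.3 = 166.4, so 167 per centre, and 167 × 3 = 501. The stated total is 513, so this is 2.3% lower: close, not exact, and only if the calculation is applied per centre. For this point it matters only that the sizing fits the unadjusted interaction, which uses baseline through change alone.

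**Precision, individually randomised contrast within homes.** With unit variance at each visit:

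- change from T1 to T2: 2(1−r) = 2 × 0.40 = 0.80
- T2 adjusted for T1: 1−r² = 1 − 0.36 = 0.64
- ratio: 0.64/0.80 = 0.80, a 20% reduction

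In general the ratio is (1+r)/2: 0.70 at r = 0.4 and 0.90 at r = 0.8, so reductions of 30% and 10%.

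**Precision, contrast between programs.** Let each home have a stable effect with variance equal to the ICC, and n residents analysed. The home effect cancels in change. In an individual-level ANCOVA without a home term, (1−r)² of it remains. The variance ratio of ANCOVA to change becomes

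(1+r)/2 + [(1−r)/2] × ICC × (n−1), which at r = 0.60 is 0.80 + 0.20 × ICC × (n−1).

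| n per home | ICC | ratio |
|---|---|---|
| 15 | 0 | 0.80 |
| 15 | 0.05 | 0.94 |
| 15 | 0.10 | 1.08 |
| 30 | 0.05 | 1.09 |

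The gain is gone once ICC × (n−1) reaches 1.

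**How often the rule would adjust.** With no true imbalance, a valid baseline test fires at its own level. A simulation (8000 runs, four groups of 90, r = 0.60, no home effects, a univariate F test standing in for the MANOVA) gave 2.7% at 0.025 and 5.2% at 0.05. Allocation of programs by home could raise this.

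**What the rule does to the result, same simulation at alpha 0.025.**

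- At an assumed effect of 0.3 SD in all three programs, power was 54% under the rule, 63% if baseline was always a covariate in the repeated-measures model, and 62.5% for ANCOVA at T2.
- The adjusted and unadjusted models disagreed on significance in 18% of those trials.
- Under the null, overall rejection under the rule was 2.2% to 2.4%, against a nominal 2.5%.
- In a separate null simulation, among trials with a baseline p-value between 0.025 and 0.10, the unadjusted test rejected in 5.1% and ANCOVA in 2.5%. This is a conditional effect.

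**If the rule fires.** In the usual repeated-measures ANCOVA the covariate has its own slope at each visit. Baseline then predicts itself exactly, so the residual variance at T1 is zero while T2 and T3 keep theirs, which conflicts with an equal-variance structure across visits.

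**The case against.** The strongest objection concerns size. The 20% belongs to a single T1-to-T2 contrast, not to the planned 4 × 3 interaction, and it compares always adjusting with never adjusting. It also presumes individual randomisation, whereas program type is randomised by home. As the table shows, modest clustering shrinks or reverses the gain for contrasts between programs. If the wait-list group is pooled across homes, contrasts against it are affected too. This stands, and it limits the figure to within-home contrasts. The simulated powers carry the same limitation.

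The double use of baseline shows no measurable loss of power: 63% against 62.5%. It is a fault of specification, not a demonstrated harm.

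Several stronger readings do not hold:

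- A reader might infer that the pre-test inflates false positives. The simulated overall rate is at or just below nominal.
- A reader might infer that the trial as a whole forgoes the equivalent of 25% more participants (1/0.80 = 1.25), about 90 on the 359 left after 30% dropout (513 × 0.7). That ignores homes, and the plan specifies intention-to-treat with multiple imputation, not an analysis of completers.
- A reader might infer that the choice is made separately for each outcome. The article names one MANOVA and does not say so.
- A reader might infer that cognitive performance can never enter. It is not named, but the conditional phrase on baseline values is broad enough that it might be meant. Nor does the article say that the MoCA is the stratifier.

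That the SAP is not shown does not answer the point, because the rule is written out in the protocol article.

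**Conclusion.** The point stands in a limited form. The article states a data-dependent covariate rule, and nowhere commits to unconditional adjustment for baseline or the stratification factors. The consequence is lost precision and a main model that is not fixed in advance; overall type I error is not at issue. At r = 0.60 the loss is about 20% of variance for individually randomised, within-home T1-to-T2 contrasts, and 10% to 30% across r = 0.8 to 0.4. For contrasts between programs it is smaller and may be nil, depending on an ICC and home size that the article does not give. The claim that the unadjusted model would usually be used assumes no true baseline imbalance. This should be changed, but it does not invalidate the trial.

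**What to change.** - Drop the MANOVA as a trigger and present baseline by group descriptively.
- In every model-based analysis, always adjust for the outcome's own baseline value and for sex, age and the cognitive measure actually used for stratification, named explicitly.
- Use follow-up values only as outcomes, with T2 adjusted for T1. Alternatively, use a constrained mixed model in which T1 is an outcome with a mean common to all groups. T2 is the comparison with a still untreated control, because the wait-list group receives the program after twelve weeks.
- Include a nursing-home term, without which the gain for contrasts between programs cannot be relied on.
- Kruskal-Wallis and Friedman tests take no covariates. For those outcomes, specify a covariate-adjusted alternative such as rank-based ANCOVA or an ordinal model.

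The cost is a rewritten analysis paragraph and slightly more analysis work. All the covariates are already collected.

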**Discussion:**

This study evaluates whether the three different interventions are feasible to reduce the decline of or even improve PA, LS, and spatial orientation in nursing home residents. By adding different training locations in *PROfit plus*, the program is expected to be superior to *PROfit basic* in increasing physical and cognitive parameters*.* Moreover, we expect the *PROfit orientation* intervention to be most effective in terms of PA, LS, and spatial orientation due to two mechanisms: (1) increased physical and cognitive activity will enhance cognitive-motor capacity and (2) the spatial training will help to build up cognitive strategies to compensate for age-related loss of spatial orientation abilities and related limitations.

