## Discussion

The overall goal of this multicentric RCT is to determine the effects of three different cognitive-motor training interventions on PA, LS, and spatial orientation in a sample of nursing home residents. We expect slower declines or even improvements in PA, LS mobility, and spatial orientation in participants of all three groups compared to wait-list controls. Regarding the secondary outcomes, we expect that physical functioning, cognitive functioning, and psychosocial well-being will be improved in all residents participating in one of the three intervention arms, when compared to the wait-list control group.

The interventions of the PROfit program combine components of exercise programs that have been proven to yield health benefits for nursing home residents [51, 93, 98, 99]. Especially the physical outcomes, e.g., walking capacity, muscle strength, and balance capacity have been shown to be improved by multicomponent interventions as conducted within the PROfit approach [91, 93, 100].

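### The only between-group test is the omnibus one; the stated follow-up tests are pre-post within each group, so no programme-versus-wait-list or programme-versus-programme hypothesis is tested directly

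*Protocol article*

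**What the plan says.** The hypotheses are comparisons between groups. The Background expects all three arms to do better in physical activity, life-space mobility and "spatial orientation compared to a wait-list control group", expects plus to beat basic, and expects orientation to do best. The Abstract repeats the ordering (of plus: "the program is expected to be superior to" basic). The Discussion repeats the comparison with control: "We expect slower declines or even improvements in PA, LS mobility, and spatial orientation in participants of all three groups compared to wait-list controls".

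Under Statistical analysis, the main model is a repeated-measures ANOVA with three test occasions and four groups ("group: PROfit basic, PROfit plus, PROfit orientation, wait-list control group"). For other data, "Kruskal-Wallis and Friedman tests instead of ANOVA will be used for non-parametrical variables". The next step is conditional ("In the case of statistically significant interaction effects") and reads: "Bonferroni-adjusted post-hoc tests (t-tests, Wilcoxon tests) will be performed to detect statistically significant differences in the groups between baseline- and post-allocation-testing". For the non-parametric version, the "probability of superiority for dependent samples) will be computed as an estimate of effect size in non-parametrical post-hoc tests".

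Three other statements matter:
- Trial design: programme type is randomised to nursing homes, and residents are randomised to intervention or wait-list within each home.
- Interventions: wait-list residents receive their home's programme after twelve weeks, that is, between T2 and T3.
- Sample size estimate: the 513 participants are derived for the test-by-group interaction.

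**The concern.** The follow-up names a contrast between two time points, inside the groups. A paired reading fits both the wording and the dependent-samples effect size. No contrast between a programme and wait-list, or between two programmes, is named.

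A significant interaction on 6 degrees of freedom says that some group's profile differs somewhere. It does not say which groups differ. It also does not say whether they differ at T2 or only at T3, after the wait-list group has itself been treated.

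The within-group tests cannot fill that gap. Retest learning, season and ageing move every group, and a significant change in one arm beside a non-significant change in another is not evidence that the two differ. The protocol also counts slower decline as success. A programme that merely holds its residents steady shows no pre-post change, so the stated follow-up cannot credit it. At stake are the statements about individual arms that the trial is designed to make.

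**Working it through.** **1. What the plan's own sample size covers.** Inputs from the Sample size estimate section: f = 0.15, alpha 0.05, power 0.95, 4 groups, 3 measurements, r = 0.60. For a within-between interaction, lambda = N f² m / (1 − r), with df1 = 3 × 2 = 6 and df2 = 2(N − 4). At N = 127, lambda = 127 × 0.0225 × 3 / 0.40 = 21.4 and power is 0.950. With 128 in equal groups, × 1.3 gives 167 per centre (501 in total) and × 1.2 × 1.1 gives 169 per centre (507 in total). Both are within 3% of 513. The figure is therefore an omnibus calculation, made per centre and multiplied by three.

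**2. Inputs for the illustration.** Completers per group: 513 × 0.70 / 4 = 89.8, taken as 90. SD of change: √(2 × (1 − 0.60)) = 0.894 baseline SD. Gate: interaction at 0.025, the level in the Statistical analysis section. Within-group alpha: 0.025/4 = 0.00625; the divisor of four is an assumption. The effect sizes are assumptions too, and clustering by home is ignored.

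**3. Shared retest gain, before the gate.** For a 0.2 SD change, z = 0.2 × √90 / 0.894 = 2.12 against a critical value of 2.734, so each group is significant with probability 0.27. Three groups with the same true change get differing verdicts with probability 1 − 0.27³ − 0.73³ = 0.59. The misleading pattern (basic or plus significant, control not) has probability 0.73 × (1 − 0.73²) = 0.34. These figures ignore the gate, so they are not the ones to use.

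**4. The same with the gate.** Simulation, 10,000 trials per row. Basic, plus and control gain 0.2 SD; orientation gains 0.2 SD plus the extra effect; all changes are held to T3.

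| Extra effect of orientation | Interaction significant | Three identical groups get differing verdicts | Basic or plus significant, control not |
|---|---|---|---|
| 0.2 SD | 21% | 11% | 7% |
| 0.3 SD | 54% | 29% | 18% |
| 0.4 SD | 85% | 48% | 28% |
| 0.5 SD | 98% | 55% | 32% |

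The last two columns are shares of all trials. On repetition with other random numbers, the third column's first entry lay between 10% and 13% and its last between 55% and 56%.

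**5. Slower decline.** Programmes unchanged; control falls 0.5 SD and stays there. The within-group test is significant in under 1% of trials for each programme, and in about 99% for control before the gate. A direct contrast of change against control at 0.025/5 (90 versus 90) detects each programme's benefit in about 82%.

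**6. What a significant interaction leaves open.** With no group difference at T2 and a 0.5 SD change in controls only at T3, it is significant in 98% of trials. With three equally effective programmes (0.35 SD) and an unchanged control, it is significant in 71%, although no programme differs from another.

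**7. Price of direct contrasts.** T2 adjusted for T1 has residual SD √(1 − 0.6²) = 0.8. At two-sided 0.025/5 = 0.005 and 80% power the multiplier is 2.807 + 0.842 = 3.649.
- All controls, 90 versus 90: 0.8 × 3.649 × √(2/90) = 0.44 SD.
- Same-home controls only, about a third of the wait-list group if evenly spread, 90 versus 30: 0.8 × 3.649 × √(1/90 + 1/30) = 0.62 SD.

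**The case against.** A reader might infer that the trial never tests intervention against control. The article does not support that. The group factor includes wait-list, the group-by-test interaction is a between-group test of change, it gates the post-hoc tests, and the sample size rests on it. Kruskal-Wallis also compares groups.

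Two further inferences go too far for the same reason:
- *Change common to all groups would be declared an effect.* If all four groups share the same change, the gate opens only at about its nominal 2.5%. The problem needs at least one group that truly differs.
- *Slower decline would go undetected.* With programmes falling 0.1 SD and control 0.5 SD, both held to T3, the interaction is significant in 85% of trials. What is lost is attribution to an arm, not detection.

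It can also be said that this is a condensed article and that detailed contrasts belong in an analysis plan that is not shown. If the article were silent on follow-up tests, that would settle the matter. It is not silent: it fixes a particular follow-up, and that follow-up does not answer the stated hypotheses. The wording for the groups is slightly loose, but the two named time points and the dependent-samples effect size point to paired tests.

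**Conclusion.** The point holds in a limited form. The plan has a valid omnibus between-group test and then attributes effects to arms by within-group tests, which cannot show that a programme beats wait-list or another programme. The size depends on the unknown effects. Under the assumptions above, identical groups get differing verdicts in about 11% to 55% of trials, and basic or plus appears effective beside a non-significant control in about 7% to 32%. If programmes hold steady while control declines 0.5 SD, the follow-up is significant in under 1% for each programme. These are individual-level illustrations with 90 completers per group and no clustering. The mismatch between the follow-up and the hypotheses rests on the text alone and needs none of these figures.

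**What to change.** Keep the omnibus test if wished. Replace the within-group post-hoc tests by pre-specified between-group contrasts of T2 adjusted for T1: basic, plus and orientation each against wait-list, plus against basic, and orientation against plus. Adjust the five by Holm or Bonferroni, and report between-group differences with confidence intervals and a between-group effect size. Keep within-group change as description.

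Programme type is assigned to nursing homes, so every contrast must account for home, and the programme-versus-programme contrasts must be presented as between-home comparisons.

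The rewording is cheap, but power is affected. The sample size covers only the omnibus interaction. Before clustering, the individual contrasts have 80% power for about 0.44 SD if all controls are used, and about 0.62 SD if only same-home controls are. The protocol should say so, state which controls each contrast uses, and not claim 95% power for the individual contrasts.
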